INTERVENTIONS

Combined aspirin (75mg od, A) dipyridamole MR (200mg bd, B) and clopidrogrel (75mg od, C) versus aspirin (75mg once daily, A) alone.

ELIGIBILTY

Inclusion criteria for patients

Age 18+

Ischaemic stroke on CT/MRI within 5 years

Previous TIA within 5 years

Written informed consent from patient or assent from a legally acceptable representative

In sinus rhythm or in atrial fibrillation but not suitable for anticoagulation

Exclusion criteria

Thrombocytopenia (platelet count<100) and or anaemia (Hb<10)

Severe hypertension SBP >180 or DBP>110 mmHg

Previous cerebral haemorrhage

Hypersensitivity or intolerance to aspirin, dipyridamole or clopidrogrel

Any history of peptic ulcer or other gastrointestinal bleeding

Severe concomitant medical conditions including AIDS or cancer

Pregnancy or breast feeding

Patients needing or already receiving anticoagulant or NSAIDS other than aspirin therapy

Involvement in another secondary prevention drug trial

Not available for follow up eg. overseas visitor

METHOD

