51 patients with a previous diagnosis of TIA or ischaemic stroke and in sinus rhythm within 5 years will be recruited into the trial. All those patients who have not previously received and tolerated dipyridamole will be given open label dipyridamole 200mg MR for a period of 2 weeks before randomisation (as per ref. EC00/08). This will be in addition to any aspirin therapy that these patients are already on. Only those patients that have completed 2 weeks without significant adverse events will continue into the trial. There will then be a 3 week washout period before participants are randomised to receive either aspirin 75mg daily or triple antiplatelet therapy. Patients with AF who are not being anticoagulated will also be enrolled in a similar manner. It is expected that the maximum follow up period for the first patient will be 15 months (maximum 2 years), ie. recruitment will take place over 12 months. Triple therapy will consist of a combination of aspirin (75mg daily), dipyridamole MR (200mg twice daily) and clopidrogrel (75mg daily). Prior to starting, all patients will have data collected relating to general demographics, risk factors, medications, smoking history, postural blood pressure measurement. In addition, a medical examination will be undertaken to find any clinical contraindications and baseline venous blood samples will be collected for the lab measures detailed below. Patients will then commence the randomised treatment regimen and be followed up after 2 weeks and then every three months (after the first 3 month follow up patients will be followed up by telephone every third month, the final follow up will be by a clinic visit). Blood tests will be repeated at 2 weeks and three months. Postural BP and pulse rate will be measured at 2 weeks, 3 months and final follow up. Screening for adverse events will occur at every follow up point. The study will continue until the last recruited patient has had their first 3 months follow up.

OUTCOME MEASURES

Primary

Number of subjects completing randomised treatment to final follow up.

Secondary

Recurrent ischaemic stroke

Recurrent TIA

Intracerebral haemorrhage

Major extracranial bleeding (clinically overt bleeding associated with one or more of; Transfusion of at least 2 units of red cells, a fall in Hb of at least 2g/l or bleeding leading to cessation of treatment.)

Minor extracranial bleeding (epistaxis, purpura)

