Sitting and standing blood pressure, heart rate at 2 weeks, 3 months and follow up.

Presence of headache

Lab Measures

Platelet Activity and leukocyte function (as in protocol approval EC00/08)

-Full blood count (Baseline, 3, 12 and 24 months)

-Platelet count

-Platelet aggregation in whole blood by single platelet counting. (hirudin as anticoagulation, ADP, PAF , collagen and AA as agonists).

-Mean platelet volume (in whole blood)

-Activated marker on platelet. (P-selectin CD62p by flow cytometry from whole blood).

-White cell platelet aggregates (CD14 on monocytes, CD11b on neutrophils and monocytes, CD42a on platelets by flow cytometry.)

SAMPLE SIZE

Assuming an overall significance (alpha) of 0.05, power (1-beta) = 0.80, 2:1 randomisation (ACD:A), and number of subjects completing treatment to end of trial is 60% in ACD group and 89% in A group3 , the required size would be 51 patients, with 17 in the aspirin group and 34 in the ACD group. Additional patients with atrial fibrillation will be enrolled during the duration of the trial up to a maximum of 30 (ACD:20, A10).

RANDOMISATION

By stratification (sinus rhythm versus atrial fibrillation) and minimisation (age, gender, time from stroke, systolic blood pressure)

REFERENCES

1 Collaborative overview of randomised trials of antiplatelet therapy, prevention of death, myocardial infarction and stroke by prolonged anti platelet therapy in various categories of patients. BMJ 1994; 308: 81-106

2 CAPRIE Steering Committee: A Randomised, blinded, trial of clopidrogrel verses aspirin in patients at risk of ischaemic events (CAPRIE). Lancet 1996; 348:1329-1339.

3 Diener HC, Cunha L Forbes C, Sivenius J Smets P, Lowenthal A: European Stroke Prevention Study 2. Dipyridamole and acetylsalicylic acid in the secondary prevention of stroke. J Neurol Sci 1996; 143: 1-13

4 EAFT (European Atrial Fibrillation Trial) Study Group. Secondary prevention in non-rheumatic atrial fibrillation after transient ischaemic attack or minor stroke. Lancet 1993;342:1255-1262.

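### The haemoglobin fall that defines a major bleed is printed in g/l, a tenth of the scale implied by the anaemia exclusion, so minor overt bleeds can be classed as major

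*Protocol*

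**What the plan says.** The Protocol's OUTCOME MEASURES section lists major extracranial bleeding among the secondary outcomes. It is defined as "clinically overt bleeding associated with one or more of" three criteria:

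- "Transfusion of at least 2 units of red cells";
- "a fall in Hb of at least 2g/l";
- "bleeding leading to cessation of treatment".

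Any one of the three is enough. The next outcome is "Minor extracranial bleeding (epistaxis, purpura"), which carries no haemoglobin limit.

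The only other haemoglobin figure in the protocol is in the exclusion criteria: "Thrombocytopenia (platelet count<100) and or anaemia (Hb<10"). No unit is printed there.

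On timing, the Lab Measures list gives "Full blood count (Baseline, 3, 12 and 24 months"). The METHOD section also says that blood tests are repeated at 2 weeks and three months.

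**The concern.** The two haemoglobin figures cannot be on the same scale. An anaemia limit of 10 g/l would exclude essentially nobody, so the exclusion is workable only in g/dl (10 g/dl = 100 g/l). The outcome definition is printed in g/l. On the eligibility scale the printed fall is 0.2, where the bare figure 2 would have meant ten times as much.

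Outcome definitions are applied literally. An assessor given this text must either accept a very small fall as sufficient or quietly substitute another threshold, and two assessors may not do the same. A nosebleed or purpura with a fall of 0.2 g/dl meets the major definition and is also named under minor bleeding, so the boundary between the two outcomes fails for such cases.

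The AIM section presents the study as an assessment of safety, tolerability and feasibility ahead of a phase 3 trial, and the groups are small. A few reclassified patients could change the picture of major bleeding that is carried forward.

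**Working it through.** **Reproducing a plan figure.** There is none to reproduce. The threshold is a definition, and no calculation in the protocol uses it.

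**Unit conversion (1 g/dl = 10 g/l).**

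- Printed threshold: 2 g/l = 2/10 = 0.2 g/dl.
- Anaemia limit, read in g/dl: 10 g/dl = 100 g/l.
- Printed fall as a share of that limit: 2/100 = 2%.
- A fall of 2 on the eligibility scale: 2 g/dl = 20 g/l, and 20/100 = 20%.
- Ratio of the two: 20/2 = 10.

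This step uses only the protocol's figures and the inference that the anaemia limit is in g/dl.

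**How often the criterion is met with no true change.** The protocol gives no haemoglobin variability, so the SD here is an assumption. Errors are taken as normal and independent.

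*Reading A:* s is the within-person SD of a single reading. The difference of two readings then has SD s√2, and P(fall ≥ t) = Φ(−t/(s√2)).

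*Reading B:* s is already the SD of the difference, and P(fall ≥ t) = Φ(−t/s).

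| s (g/dl) | A: t = 0.2 g/dl | A: t = 2 g/dl | B: t = 0.2 g/dl | B: t = 2 g/dl |
|---|---|---|---|---|
| 0.2 | Φ(−0.707) = 24% | Φ(−7.07), negligible | Φ(−1) = 16% | Φ(−10), negligible |
| 0.4 | Φ(−0.354) = 36% | Φ(−3.54) = 0.02% | Φ(−0.5) = 31% | Φ(−5), negligible |
| 0.6 | Φ(−0.236) = 41% | Φ(−2.36) = 0.9% | Φ(−0.333) = 37% | Φ(−3.33) = 0.04% |

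With a larger single-reading SD of 0.8 g/dl, reading A gives 43% for 0.2 g/dl and 3.9% for 2 g/dl. The statement that 2 g/dl is met in under 1% of cases therefore holds for an SD up to 0.6 g/dl and not for any SD whatever. The contrast between the thresholds remains.

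These are probabilities per overt bleed that has a count before and after it. They are not expected numbers of events.

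**Weight of one reclassified patient.** The SAMPLE SIZE section plans 34 on triple therapy and 17 on aspirin, plus up to 20 and 10 with atrial fibrillation.

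- Sinus rhythm only: 1/34 = 2.9 and 1/17 = 5.9 percentage points.
- With the full atrial fibrillation group: 1/54 = 1.9 and 1/27 = 3.7 percentage points.

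**Reach.** The primary outcome is the number completing randomised treatment, and the sample size rests on completion of 60% against 89%. Neither uses the haemoglobin threshold.

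**The case against.** Several objections can fairly be made.

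- **The bleed must be overt.** A haemoglobin drop alone does not qualify, and epistaxis and purpura are named as minor. This stands. A reader might infer that trivial bleeds will all be counted as major; the text supports only that some can be.
- **Few bleeds may have paired counts.** After the 3-month visit, follow-up is by telephone until a final clinic visit, and scheduled full blood counts are sparse. This stands as a limit: the number of affected events cannot be estimated from the protocol.
- **The variability is assumed.** This stands. Only the factor of ten comes from the document. That a 0.2 g/dl fall lies within ordinary variation is a consequence of the assumed SD, not something the protocol states.
- **The companion criteria do not settle the intended severity.** Transfusion of two or more units sits beside bleeding that stops treatment, which has no blood-loss floor. This stands, so the transfusion criterion is weak evidence of what was meant. The conflict with the eligibility scale does not depend on it.
- **Bias between arms is not shown.** A reader might infer that major bleeds on triple therapy would be inflated disproportionately. With the same false-major probability p per bleed in both arms, b₁ and b₂ minor bleeds add p·b₁ and p·b₂ events, in the same ratio as the minor bleeds themselves. The absolute gap would widen if triple therapy causes more minor bleeds, but the protocol gives no bleeding rates for either arm.
- **It is not labelled the main safety outcome.** A reader might infer this from the study's title, but the protocol lists major extracranial bleeding as one of several unranked secondary outcomes.

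None of these removes the discrepancy. Nothing elsewhere in the protocol corrects or explains the unit.

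**Conclusion.** The major-bleed threshold is wrong as written, or at the least unreconciled with the protocol's own haemoglobin scale. This is a unit inconsistency in an outcome definition rather than a failed calculation. The printed threshold is one tenth of what the same figure would mean on the eligibility scale. That conclusion rests on one inference, that the anaemia limit is in g/dl, and no other reading makes the exclusion workable.

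For an overt bleed with paired counts, the illustrated chance of meeting the criterion with no true change is 24% to 41% for a single-reading SD of 0.2 to 0.6 g/dl, or 16% to 37% if that is the SD of the difference. For 2 g/dl it is under 1% on either reading. The consequence is a blurred major/minor split in a secondary safety outcome.

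It might also be inferred that 2 g/dl was certainly intended. The exclusion criterion shows which scale the protocol uses there, but does not prove what the outcome threshold was meant to be. Only the sponsor can confirm that.

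**What to change.** Reconcile the haemoglobin unit in the secondary outcome definition with the scale used in the exclusion criteria. The sponsor should confirm the intended threshold (2 g/dl, equal to 20 g/l, if that is what was meant) and print the unit in both places. This should be done before any bleeding event is classified, because a change made once arm-level data are known would look post hoc.

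The cost is an amendment of about one word in each place, with no effect on the primary outcome, the sample size or the visit schedule. The downside is that, if the threshold is confirmed as 2 g/dl, fewer events will be called major.

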COMBINED ASPIRIN, CLOPIDROGREL AND DIPYRIDAMOLE VERSUS ASPIRIN ALONE IN STROKE SECONDARY PREVENTION; A SAFETY TOLERABILITY AND FEASIBILTY STUDY

BACKGROUND

Stroke is a leading cause of long term disability and death around the world. Increased platelet activity plays a critical role in the physiology of stroke. The key medical strategy for the secondary prevention of stroke is anti-platelet therapy. Several antiplatelet agents have been used which inhibit different pathways of platelet activation. The earliest agent aspirin, a cyclo-oxygenase inhibitor, showed a reduction of relative risk for stroke recurrence of approximately 25% compared with placebo1. The newly developed ADP receptor blocker clopidrogrel, showed a slight benefit over aspirin2. Dipyridamole, a phosphodiesterase inhibitor and modulator of adenosine uptake, is an effective preventative agent when used alone after stroke3. Furthermore the combination of aspirin and dipyridamole was superior to either agent alone3. The European Atrial Fibrillation Trial4 found that warfarin was superior to aspirin in the secondary prevention of stroke in patients with cardioembolic cerebral ischaemia due to atrial fibrillation. However, clinical practice reveals that between 50-66% of stroke survivors are unable to take warfarin, mostly for reasons of contraindication or problems with regular monitoring of anticoagulation. We hypothesise that combination therapy with three antiplatelet agents that act through different mechanisms may maximise the benefit of antiplatelet treatment in the secondary prevention of stroke, both in patients with sinus rhythm and those with stroke who cannot be anticoagulated. In a laboratory study we found that triple antiplatelet therapy was superior to double or monotherapy in respect of inhibiting invitro platelet function, leukocyte function and the formation of platelet leukocyte conjugates5 . Provisional data from an ongoing pilot study in normal subjects and patients with previous ischaemic stroke (ethics no. EC00/08) support the concept that triple therapy is most effective in inhibiting platelet and leukocyte function ex vivo (unpublished data).

AIM

To assess the safety, tolerability and feasibility of administering triple antiplatelet therapy (aspirin, dipyridamole, and clopidrogrel) in comparison with aspirin. This study is the prelude to a large phase 3 trial to be submitted to the MRC for funding.

DESIGN

Prospective, pilot, randomised, parallel group trial.

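### Stopping treatment is enough to make a bleed major, so one nosebleed or purpura can count as both major and minor and, if the stop is permanent, against the primary outcome

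*Protocol*

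**What the plan says.** Under Outcome Measures, Secondary, the protocol defines major extracranial bleeding as "clinically overt bleeding associated with one or more of" three criteria: a transfusion of at least two units of red cells, a haemoglobin fall of at least 2 g/l, or "bleeding leading to cessation of treatment". Each criterion is sufficient alone. The third carries no condition on the site, amount or duration of the bleed, and does not say whether a temporary stop counts.

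The next item reads "Minor extracranial bleeding (epistaxis, purpura", and its definition ends there. Nothing says that a bleed meeting a major criterion is left out of the minor category.

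The primary outcome is "Number of subjects completing randomised treatment to final follow up".

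Interventions sets the three-drug combination "versus aspirin (75mg once daily, A) alone", and Design describes a "Prospective, pilot, randomised, parallel group trial". Neither section mentions placebo, blinding or blinded assessment of events. The protocol uses the term open label only for the dipyridamole run-in (Method).

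**The concern.** A severity grade should describe the bleed. Here one route to the grade of major describes what the patient or doctor did afterwards. This has three consequences.

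- A nosebleed or purpura that prompts stopping falls into two categories that a reader would take to be exclusive.
- A permanent stop for such a bleed is counted again in the primary outcome, so the safety and tolerability comparisons share some events.
- A decision to stop can be influenced by knowing that the patient takes three antiplatelet drugs. Transfusion is less exposed to this, and a measured haemoglobin fall much less.

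The Aim section presents the study as an assessment of safety, tolerability and feasibility ahead of a phase 3 trial. A major-bleeding rate that mixes transfused bleeds with nosebleeds that led someone to stop tablets would be hard to use for that purpose.

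**Working it through.** The protocol gives no expected bleeding rate, so there is no figure to reproduce. The check is to apply the definitions as printed to a set of events.

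| Overt extracranial event | Major? | Minor? | Fails primary outcome? |
|---|---|---|---|
| Nosebleed or purpura; no transfusion or qualifying haemoglobin fall; treatment continues | No | Yes | No |
| Same, with a temporary stop | Yes, if a temporary stop is a cessation (not stated) | Yes | Not necessarily |
| Same, with a permanent stop | Yes, by cessation alone | Yes | Yes |
| Nosebleed with a two-unit transfusion; treatment continues | Yes, by transfusion | Yes | No |
| Any patient who stops permanently for a reason other than bleeding | No | No | Yes |

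Rows 2 and 3 show the double classification caused by the cessation clause. Row 4 shows that the overlap has a second source, the missing exclusion in the minor definition, so deleting the clause alone would not make the categories exclusive. Row 5 shows why the overlap with the primary outcome is only partial.

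**How many patients.** The Sample Size section assumes completion of "60% in ACD group and 89% in A group3" (the final 3 is a reference number), with 34 and 17 patients. Expected non-completers are:

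- triple therapy: (1 − 0.60) × 34 = 13.6
- aspirin: (1 − 0.89) × 17 = 1.87

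These counts cover all reasons for not completing. The number shared between major bleeding and the primary outcome is therefore some fraction of them, from 0 to 13.6 and from 0 to 1.87, and the documents do not give that fraction. Purely as an illustration, assume that 20% to 50% of non-completers in each arm stop for a bleed that meets neither the transfusion nor the haemoglobin criterion:

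- triple therapy: 0.2 × 13.6 = 2.7 to 0.5 × 13.6 = 6.8, or 8% to 20% of 34
- aspirin: 0.2 × 1.87 = 0.4 to 0.5 × 1.87 = 0.9, or 2% to 6% of 17

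The share is an assumption, as is its equality across arms, and the up to 30 additional patients with atrial fibrillation are left out.

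**The haemoglobin criterion.** Exclusion criteria gives an anaemia threshold of haemoglobin below 10 without a unit, whereas the bleeding definition uses a fall of 2 g/l. If the 10 is in g/dl (an assumption), then 2 g/l ÷ 10 = 0.2 g/dl, or 0.2 ÷ 10 = 2% of that threshold. As printed, this criterion may also admit trivial bleeds.

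**The case against.** The strongest reply is that counting a bleed that ends treatment as major is a cautious choice in a safety pilot, that the outcome is secondary, and that the sample size rests on completion alone. A statistical analysis plan, which is not at hand, could set precedence between categories and tabulate each component. Much of this is fair, and it limits the seriousness of the point. But a precedence rule would only settle that the nosebleed is major. It would not change the fact that the protocol grades it so on a decision to stop.

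Three stronger readings may tempt a reader, and the documents do not support them.

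- *Major bleeding duplicates the primary outcome.* It does not. The primary outcome counts stops for any reason. The protocol also lists headache as an outcome, so intolerance other than bleeding is foreseen.
- *The trial is open label and the comparison is biased against triple therapy.* The protocol does not say that the randomised phase is unblinded, and a lower stopping threshold on triple therapy is conjecture. Any such bias would also act on the primary outcome and on a separate outcome of discontinuation for bleeding, so rewording the definition would not remove it. It would only keep it out of the severity grade.
- *An excess of 8–20% against 2–6% is to be expected.* Those percentages are an assumed share multiplied by planning rates and are not evidence.

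The objection that deleting the cessation clause would not by itself separate the categories, and would leave a doubtful haemoglobin threshold in place, is correct. The fix takes in both.

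**Conclusion.** The point holds as a fault in a stated definition. As printed, a nosebleed or purpura that prompts stopping is both a major and a minor bleed, and a permanent stop also counts against the primary outcome. This follows from the wording and needs no assumption about rates.

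The overlap with the primary outcome is limited to permanent stops for bleeding. The greater exposure to bias rests on inferring from silence that treatment is known. The number of patients affected cannot be derived. With planned arms of 34 and 17, each reclassified patient moves the major-bleeding rate by 1/34 = 2.9 or 1/17 = 5.9 percentage points, so a few would matter.

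The sample size and the primary outcome are unaffected. The definition should be corrected because bleeding is a central safety measure in a pilot meant to inform phase 3. The fault does not undermine the trial.

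**What to change.** Make four linked edits in Outcome Measures, Secondary:

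1. Classify major extracranial bleeding by the transfusion and haemoglobin criteria only.
2. Report bleeding leading to discontinuation as its own outcome, by arm, and state whether temporary stops count.
3. Define minor as extracranial bleeding that does not meet the major definition, with nosebleed and purpura as examples. This wording is what makes the categories exclusive.
4. State the haemoglobin unit in both the bleeding definition and the exclusion criterion, and reconcile the two figures. Without this, the retained criterion may itself class trivial bleeds as major.

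The same data are collected and the sample size does not change. The cost is that fewer events will be classed as major. Because contact after the three-month visit is by telephone until the final clinic visit, some bleeds in that period will have no haemoglobin measurement close to the event. Those that led to stopping will still appear in the separate discontinuation outcome.

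### The claimed 80% power for 51 patients holds only under an unstated one-sided, unpooled calculation; a two-sided 5% chi-square test has about 58%

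*Protocol*

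**What the plan says.** The primary outcome (Outcome Measures) is "Number of subjects completing randomised treatment to final follow up", a binary measure for each patient. The Sample Size section sizes the trial on it. The inputs are "Assuming an overall significance (alpha) of 0.05", "power (1-beta) = 0.80", allocation of two triple-therapy patients to each aspirin patient, and "number of subjects completing treatment to end of trial is 60% in ACD group and 89% in A group". The conclusion is that "the required size would be 51 patients, with 17 in the aspirin group and 34 in the ACD group".

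No test, variance formula or sidedness is given. No inflation for dropout is given either, and none is needed, because non-completion is itself the outcome.

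The Method section describes the same number as sinus-rhythm patients: "51 patients with a previous diagnosis of TIA or ischaemic stroke and in sinus rhythm within 5 years will be recruited into the trial". Patients with atrial fibrillation (AF) come on top, up to 30 of them (20 triple, 10 aspirin), and are not part of the calculation. Rhythm is a stratification factor in the Randomisation section.

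**The concern.** An alpha of 0.05 given without qualification is normally read as two-sided. On that reading the stated inputs need clearly more than 51 patients, and 51 patients fall short of the stated power under every two-sided method tried.

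The comparison affected is the primary one, in a study that the Aim section presents as the forerunner of a large phase 3 trial. With a two-sided 5% chi-square test, a true 29-point drop in completion would go undetected about 42% of the time (1 − 0.585), where the protocol implies 20%. Anyone using the protocol to judge what a non-significant difference in completion can exclude would be working from the wrong figure.

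**Working it through.** **Inputs** (all from the Sample Size section): p_A = 0.89, p_T = 0.60, d = 0.29, d² = 0.0841, n_T = 2·n_A, alpha 0.05, power 0.80. The z values are 1.960 (two-sided 5%), 1.645 (one-sided 5%) and 0.842 (80% power).

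**Step 1: reproduce 51.** With unpooled variance,

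n_A = (z_α + z_β)² · V / d², where V = 0.89×0.11 + 0.60×0.40/2 = 0.0979 + 0.1200 = 0.2179.

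One-sided: n_A = (1.645 + 0.842)² × 0.2179 / 0.0841 = 16.02. This rounds up to 17, so 17 + 34 = 51, the stated figure. The unrounded total is 48.06; the match appears only after rounding up to whole 1:2 arms.

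**Step 2: the other standard formulas.**

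- Unpooled, two-sided: (1.960 + 0.842)² × 0.2179 / 0.0841 = 20.34.
- Pooled: n_A = [z_α·√(1.5·p̄(1−p̄)) + z_β·√V]² / d², with p̄ = (0.89 + 2×0.60)/3 = 0.6967 and p̄(1−p̄) = 0.2113. Two-sided: (1.960×0.5630 + 0.842×0.4668)² / 0.0841 = 26.6.
- Arcsine: n_A = 1.5·(z_α + z_β)² / h², with h = 2·asin√0.89 − 2·asin√0.60 = 0.693. Two-sided: 24.49.
- Pooled with continuity correction: n_A′ = (n_A/4)·[1 + √(1 + 6/(2·n_A·d))]². Two-sided: 31.6.

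| Formula | Two-sided 5% | One-sided 5% |
|---|---|---|
| Unpooled | 20.34 → 21:42 = 63 | 16.02 → 17:34 = **51** |
| Arcsine | 24.49 → 25:50 = 75 | 19.29 → 20:40 = 60 |
| Pooled | 26.6 → 27:54 = 81 | 20.7 → 21:42 = 63 |
| Pooled, continuity corrected | 31.6 → 32:64 = 96 | 25.6 → 26:52 = 78 |

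Only one of the eight cells gives 51.

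**Step 3: power at 17:34.** The standard error under the alternative is √(0.0979/17 + 0.2400/34) = 0.1132. Under the pooled null it is √(0.2113×(1/17 + 1/34)) = 0.1366.

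- Two-sided pooled: Φ[(0.29 − 1.960×0.1366)/0.1132] = Φ(0.20) = 57.8%.
- Two-sided unpooled: Φ(0.29/0.1132 − 1.960) = Φ(0.60) = 72.6%.
- One-sided unpooled: Φ(0.29/0.1132 − 1.645) = Φ(0.92) = 82.0%.

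The exact values below come from enumerating both binomial distributions.

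| Test at 17:34 | Two-sided: approximate / exact | One-sided: approximate / exact |
|---|---|---|
| Chi-square (pooled) | 57.8% / 58.5% | 71.8% / 74.1% |
| Fisher | – / 52.4% | – / 62.4% |
| Unpooled Wald | 72.6% / 71.6% | 82.0% / 80.6% |
| Arcsine | 64.6% / – | 75.5% / – |
| Chi-square, continuity corrected | – / 43.9% | – |

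**Step 4: does the reproducing test hold 5%?** Exact type I error at 17:34, for common completion rates of 60%, 70%, 80% and 89%:

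- one-sided unpooled Wald: 6.7%, 7.3%, 7.2%, 11.0%;
- one-sided pooled: 4.8%, 4.9%, 4.7%, 4.7%;
- two-sided unpooled Wald: 6.7%, 6.7%, 7.0%, 8.7%.

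So the 80.6% is obtained with a test that exceeds the stated alpha. The same holds for the most favourable two-sided figure, 72%.

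**Step 5: the AF patients.** If all 30 enrolled, the arms would be 17 + 10 = 27 and 34 + 20 = 54, total 81. Two-sided pooled power is then 80.6% (exact 82.2%). A simulated rhythm-stratified Cochran-Mantel-Haenszel test gives 82.2%, assuming the same completion rates in both rhythm strata.

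**The case against.** The strongest reply is that the number reproduces. The protocol does not say two-sided, and its own inputs give exactly 17:34 under a one-sided 5% calculation with unpooled variance. A one-sided question is not far-fetched here: the assumed direction is fixed at 60% against 89%, and the aim is safety, tolerability and feasibility in a pilot. Two-sidedness is therefore something the reader brings, and the size of the shortfall depends on the test chosen.

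Much of this stands. A reader might infer that 51 is simply a miscalculation and that the true power is 58%. The document does not support that: 58% belongs to one test on one reading, and 51 has an exact derivation. That this derivation was the one used is itself only inferred from the match.

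A reader might also infer that a non-significant result will be taken as evidence of tolerability. The protocol sets no such rule and no significance-based criterion for going on to phase 3.

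Finally, a reader might notice that 51 + 30 = 81 equals the two-sided pooled requirement and conclude that the trial is adequately sized overall. The Sample Size section treats the AF patients as additional and only up to a maximum, and it attaches the 80% to 51.

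What does not stand is the idea that the one-sided route makes the statement sound. The protocol never says one-sided, the test concerned does not keep to 5% at this size, and the one-sided pooled test that does has about 74% power. Nor can the matter be left to a statistical analysis plan, because the protocol itself fixes alpha, power, rates and sample size.

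**Conclusion.** The power statement is wrong as written. On the conventional two-sided 5% reading, 51 patients do not deliver 80%: exact power is about 58% (chi-square), 52% (Fisher) or 72% (unpooled Wald), and 80% needs 63 to 81 patients in whole arms, or 96 with a continuity correction. On a one-sided 5% reading, 51 is reproduced only with unpooled variance, at an actual type I error of about 6.7% to 11%.

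That the statement needs correcting does not depend on the choice of formula; the size of the gap does. All figures take the protocol's 89% and 60% as given. The type I error range assumes common completion rates between 60% and 89%.

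**What to change.** In the Sample Size section, name the test and the sidedness, and restate the power of 51 patients (17:34) to match, without changing enrolment:

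- if a two-sided 5% chi-square test is intended, about 58%;
- if a one-sided 5% test was intended, say so and give about 74% for the pooled test.

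Do not count the AF patients towards this figure unless the primary comparison is prespecified as a rhythm-stratified analysis of all randomised patients. In that case, state that about 80% two-sided power applies only if all 30 are enrolled and completion rates are the same in both strata. The protocol supports neither condition, so this should not be the main remedy.

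The change is to wording only and needs no extra patients. Its cost is a less favourable stated power.
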